### Statistical analysis

Descriptive statistics will be used to present group characteristics on age, sex, body mass index, base of support width (BSW) [86, 87], and history of falls, activity of daily live, physical activity habits, and risk factors for falls.

According to statistical criteria of termination of the trial, we have no predefined stopping rules because we are not expecting risks that are different in the groups (i.e. no adverse event stopping criteria).

We will use an intention-to-treat analysis based on all randomized patients, with missing values and dropouts replaced by multiple imputation methods, as recommended by current guidelines on randomized controlled trials [88].

The primary analysis will be done to test for the incidence of falls. We follow the proposition of Röhmel and Pigeot [89], who showed that superiority of the experimental group (“T&E” in our case) over the reference treatment (“Otago” in our case) can be tested after successfully demonstrating non-inferiority (if stated a-priori in the protocol). To simultaneously demonstrate superiority of E (T&E) to R (Otago) and R (Otago) to P(Helsana) as well as the non-inferiority of E (T&E) to R (Otago), we will use negative binomial regression [90, 91] and follow an approach proposed by Mütze et al. [84]. A sensitivity analysis without multiple imputations of missing values will be performed.

For the primary analyses, we will adjust for the participants’ length of observation, center, age and risk for falls category [92]. We will perform a per protocol sensitivity analysis including time varying co-variables to reduce confounding and selection bias, e.g. due to differential censoring.

Further analyses will be performed to test the secondary endpoints quality of life (Overall score of OPQOL-35), severity of falls (Schwenk Scale), fear of falling (FES-I), functional capacities (TUG, FSBT, FTSTS, FR and SMWT), as well as adherence to the exercise recommendations (duration in min/week, frequencies/week).

We will perform a subgroup analysis based on age groups to test the secondary hypothesis that compliance in older group is better with the Otago compared to T&E and that in younger participants’ compliance is better in T&E compared to Otago.

The data monitoring committee will do interim analyses only for data quality evaluation and for monitoring of adverse events, i.e. no interim for effectiveness will be performed. The results of this analyses will be accessible for the steering committee.

The proportion of adverse events (other than falls) will be compared between the groups by an external and independent statistician.

All deviations from the statistical plan will be documented and an amendment will be sent to the ethical commissions as well as to Protocol Registration System ClinicalTrials.gov. The deviations from plan to actual analysis will also be reported in the final publication(s).

We will use multiple imputation methods using 50 imputed datasets under the assumption that missing data are missing at random. We will run sensitivity analyses to test the robustness of our replacement models and the robustness of the assumption “missing at random”.

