### Participants

The population consists of older adults > 65 years, living in their own home and identified as at-risk of falling. Table 1 shows the inclusion and exclusion criteria.

**Table 1 Tab1:** Inclusion and exclusion criteria

Inclusion criteria	Exclusion criteria
Older adults aged ≥ 65 years living independently at home	Severe vision impairments that do not permit the reading of the exercise-programme booklet and that do not permit the completing of the monthly diaries
Able to walk without mobility aids in their home	In physiotherapy treatment that trains balance
History of fall in the previous 12 months or perceiving fear of falling (≥ 20 points [98] on FES-I [63])	Cognitive impairment (< 24 points [99] on the Minimal Mental State Examination [100])
Good understanding of the Trial language (French or German)	Contraindication given by the referring physician

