### Recruitment, randomization, blinding and treatment allocation

Caregivers (medical doctors, nurses, physiotherapists) in partner hospitals, health-care centres and medical offices will recruit the participants. To achieve adequate enrolment to reach target sample size, we projected to enrol a quarter of the sample size in each region (101/region) for three years (from August 2016 to September 2019). In addition, the local coordinators will meet the recruitment partners twice a year. They will give a feed-back about the progress state on the trial and motivate them to continue the recruitment.

The local coordinators will verify the eligibility criteria (Table 1) at the home of the participants.

The final decision on inclusion or exclusion and randomization takes place after the baseline assessment. A researcher who is not involved in the study creates an allocation list with a computer generated random sequence using the command “ralloc” within Stata (StataCorp, college Station, Texas, USA), version 14.2. A block-randomization is executed stratified in groups of age (65–79; > 80 years old) and in risk of fall categories [51] (low-moderate; high). If a couple living in the same house will participate, both persons will be randomized in the same intervention group [52].

The randomization was integrated in the software for Research Electronic Data Capture (REDCap [53]) and is concealed to all members of the research team. The project assistant manually triggers the randomization after the baseline assessment. The local coordinators will take note of the allocation group in REDCap.

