### Outcomes

The primary outcome “falls incidence” and exercise frequency will be assessed prospectively and for twelve months with self-recorded monthly diaries. If a patient decides to stop his participation (completing monthly diaries and exercise training), the physiotherapist will ask him to participate at the intermediary or/and finale assessment. Physiotherapist-assessors who are unaware of group allocation (“blinded assessors”) will assess the secondary outcomes at baseline, at the six-month intermediary assessment, and at the twelve-month final assessment. All assessors are independent physiotherapists and specially trained to perform the assessments.

To ensure that the assessors remain unaware of the group allocation, patients are told not to talk about their treatment with the assessor.

The main outcome is the incidence of falls for twelve months. For this study we define a fall as “*an unexpected event in which the participant comes to rest on the ground, floor, or lower level, with or without injury*” as recommended in the systematic review of Hauer et al. [59]. The history of falls (number, circumstance (Where? *Inside OR outside;* When? *Day OR night;* How? *Describe shortly the event*) and severity) in the previous twelve months will be assessed at baseline. During the study, falls will be prospectively self-reported (number, date, circumstance and severity) in monthly diaries [60]. To ensure that the patients complete the diaries, the physiotherapists will check them at each visit and ask about the diaries during each phone call [59]. In addition, falls events (number, circumstance and severity) will be asked during the intermediary assessment and at the final assessment. The diaries will be sent to the coordinators. The coordinators will send them in PDF version to the project-assistant. She will enter the data in REDCap software once a month.

Secondary outcomes include severity of falls, fear of falling, gait, strength and balance and quality of life. They will be assessed at baseline, at the intermediary assessment and at the final assessment. They also include exercise-adherence. This outcome will be assessed at twelve months.

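### The primary falls model leaves out the baseline count of previous falls: a missed gain in precision, not a validity error

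*Protocol article*

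**What the plan says.** The Statistical analysis section of the protocol article tests fall incidence over twelve months by negative binomial regression and adjusts for "length of observation, center, age and risk for falls category". The list is closed; it is not introduced as a set of examples.

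The Recruitment, randomization, blinding and treatment allocation section stratifies by age group and "in risk of fall categories [51] (low-moderate; high"). The category therefore has two levels, and its definition is left to a citation.

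The Outcomes section collects past falls: "The history of falls (number, circumstance" and severity, "in the previous twelve months will be assessed at baseline". The order of events is clear: "The final decision on inclusion or exclusion and randomization takes place after the baseline assessment". The count is therefore known before allocation.

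The only analytic use stated for it is descriptive. The Statistical analysis section lists the group characteristics as age, sex, body mass index, base of support width, "and history of falls, activity of daily live, physical activity habits, and risk factors for falls".

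Table 1 under Participants admits people by either of two routes: "History of fall in the previous 12 months or perceiving fear of falling". A participant may therefore enter with no past fall or with several.

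**The concern.** In a negative binomial model, the variance of a log rate ratio has a Poisson part, set by the expected number of falls, and a part set by stable differences between people. Only the second part can be reduced by covariates. A person's own count of falls over the previous year is an obvious candidate for that, and the trial already records it.

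The listed risk category may capture some of this, but two levels cannot carry a whole count. Whatever the count would explain beyond the category stays in the dispersion and widens the interval. The primary analysis has to support a non-inferiority claim with a 5% margin and two superiority claims, with 81 people in the smallest arm, so some precision may be forgone for want of one model term.

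**Working it through.** **Inputs from the Sample size section.** Fall rates are 0.50 (T&E), 0.79 (Otago) and 0.92 (Helsana). The arms are 162/162/81, with 15% dropout.

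**Inputs that are not in the document and are assumed here.** Dispersion φ is 1 or 2. Mean number of prior falls is 0.92. Persistence of fall propensity from the prior year to the study year is 0, 0.3, 0.6 or 0.9.

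**Step 1: the plan's own figure.** 405 × 0.85 = 344.25. By arm, 162 × 0.85 = 137.7 and 81 × 0.85 = 68.85, so about 138/138/69 are analysed. The dropout step reproduces. The 344 itself is neither confirmed nor refuted, because dispersion, sidedness and margin scale are not given. A 95% retention-of-effect contrast gives 344 at φ = 0.90 (one-sided 5%) or φ = 0.40 (one-sided 2.5%). A rate-ratio margin of 1.05 gives 344 at φ = 1.22 or 0.61. The planned dispersion therefore cannot be recovered from the sample size.

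**Step 2: what a covariate can change.** With one year of observation each,

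Var(log RR, T&E vs Otago) = (1/0.50 + 1/0.79 + 2φ)/138 = (3.266 + 2φ)/138.

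At φ = 1 this is 5.266/138 = 0.0382, an SE of 0.195. If the prior count explains a share s of the dispersion, the variance ratio is (3.266 + 2φ(1 − s))/(3.266 + 2φ). At φ = 1:
- s = 10%: 5.066/5.266 = 0.962
- s = 25%: 4.766/5.266 = 0.905

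The Poisson term, 3.266, is untouched, which limits the gain.

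**Step 3: simulation.** Negative binomial regression was fitted with 138/138/69 analysed and 400 runs per scenario, with and without log(1 + prior falls). Prior and on-study falls were linked by correlated log-normal frailties, so the fitted SEs differ somewhat from the formula in step 2. The variance ratio is the squared ratio of median SEs. The equivalent number of extra analysed participants is 344/ratio − 344; for example, 344/0.961 − 344 = 14.

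| Risk category | φ | Correlation, prior vs on-study falls | Variance ratio | Equivalent extra participants |
|---|---|---|---|---|
| No fall history | 1 | 0.00 | 1.002 | −1 |
| No fall history | 1 | 0.10 | 0.990 | 3 |
| No fall history | 1 | 0.22 | 0.961 | 14 |
| No fall history | 1 | 0.37 | 0.904 | 36 |
| No fall history | 2 | 0.00 | 1.004 | −1 |
| No fall history | 2 | 0.11 | 0.985 | 5 |
| No fall history | 2 | 0.28 | 0.940 | 22 |
| No fall history | 2 | 0.49 | 0.822 | 74 |
| Encodes ≥ 2 prior falls | 1 | 0.21 | 0.985 | 5 |
| Encodes ≥ 2 prior falls | 1 | 0.37 | 0.969 | 11 |
| Encodes ≥ 2 prior falls | 2 | 0.28 | 0.983 | 6 |
| Encodes ≥ 2 prior falls | 2 | 0.49 | 0.929 | 26 |

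The spread of the estimates across runs shows the same direction but is noisier, with ratios from 0.999 down to 0.72.

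Where the category carries no history, power for T&E versus Otago superiority rises by about 0–1 point at low to moderate correlation, and by about 5 points (φ = 1) to 9 points (φ = 2) at the highest. Where the category encodes repeat falls, the change runs from −3 to +3 points. Monte Carlo error on each power is about 2.5 points, so the small changes cannot be told from zero.

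**Step 4: Otago versus Helsana.** At φ = 1 the variance is (1/0.79 + 1)/138 + (1/0.92 + 1)/69 = 0.0164 + 0.0302 = 0.0467, an SE of 0.216. The effect is log(0.92/0.79) = 0.152, so z = 0.70 and power at one-sided 2.5% is about 10%. With all dispersion removed (φ = 0), the variance is 0.0092 + 0.0158 = 0.0249, the SE is 0.158, z = 0.96 and power is about 16%. In the simulations, power was about 9–14% with or without the covariate.

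**The case against.** The strongest reply is that nothing in the list is wrong. It contains exposure, site and both stratification factors, which is a coherent set matched to the design, and it gives a valid randomised comparison. That stands, and it limits the point to efficiency.

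A second reply is that the risk category may already contain fall history. It is defined only by citation, so this cannot be settled here. Table 1 shows that past falls vary across participants, not how far they vary within a risk level. This also stands, and it is why the smaller range is given beside the larger one. It does not remove the point, because a binary category cannot hold the full count.

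Third, the size depends on assumptions. The simulations model neither selection at entry, where many people join because they recently fell, nor error in twelve-month recall, which would dilute the gain. This stands as well.

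Three stronger readings are tempting and are not supported:
- **Bias.** A reader might infer that chance imbalance in past falls, especially in the 81-person arm, would bias the result. Randomisation is stratified by risk category and the model adjusts for it. Remaining chance imbalance is already reflected in the standard error.
- **Secondary outcomes.** A reader might infer that these also lack baseline adjustment. The article states no models for them and excludes nothing; such detail is normally left to the analysis plan.
- **No cost.** A reader might think the change is free. The Statistical analysis section requires deviations to be documented, sent as an amendment to the ethics commissions and the registry, and reported in the final publication.

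**Conclusion.** The point holds as a missed efficiency gain. The primary adjustment set omits a baseline count that is collected before randomisation and is otherwise used only descriptively. With a log link and no treatment-by-covariate interaction, adding the count leaves the target rate ratio unchanged. It costs next to nothing in precision even if the count proves uninformative (variance ratios 1.002 and 1.004 at zero correlation).

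The size cannot be fixed from the document. With φ of 1 to 2 and correlations from 0 to about 0.5, variance falls by roughly 0–18% if the risk category carries no fall history, and by about 1–7% if it already separates repeat fallers. The upper ends need a highly persistent fall propensity; the lower ends are small enough to go unnoticed. The change does not make Otago versus Helsana adequately powered, since under the planned rates even removing all dispersion would not.

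**What to change.** Before unblinding, pre-specify log(1 + number of falls in the previous 12 months) as an additional covariate in the primary negative binomial model, and keep length of observation, centre, age and risk category as they are. No change to data collection or sample size is needed.

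The cost is one model parameter and a documented amendment by the route that the Statistical analysis section already sets out. Pre-specification matters because a covariate added after the allocation is known would look chosen for its result.

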**Fig. 1 Fig1:**
[figure not shown]
Recommendations for create your home-based exercise-programme

Physiotherapy treatment is focused on increasing motivation and exercise adherence, working on the self-efficacy, the self-confidence and the autonomy of the patients. The implementation of the T&E programme is planned with eight physiotherapy sessions and four phone calls in six months. At each session the physiotherapists revise the exercises execution, verify that the diaries are correctly completed and repeat the recommendations for the training. At each phone call, the physiotherapists ask about the exercises, if the patient encounter difficulties and encourage them to train themselves.

The physiotherapists for the implementation of the T&E programme are trained in a basic training of half a day. The training focuses on i) Encouragement of the autonomy of the participant, ii) The significance of the evaluation of the perceived difficulty, iii) The work as coach for the participant, iv) Stimulation for exercises adherence: not too much at the same time, but regularly, v) Safety of the environment where the patient will train, vi). All physiotherapists will participate in a yearly refresher course and experience sharing session.

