### Control interventions

To evaluate the T&E programme, we will compare it with two established interventions.

The first intervention consists of the implementation of the Otago exercise programme (OEP) [57]. This programme was developed in New-Zeeland in the 2000’s to prevent falls in older adults. It contains 22 exercises: five for warming-up, five for muscle strengthening of the lower limbs and twelve for balance training. In addition, it recommends walking sessions between the training days. OEP shows significant results in reducing the risk of death and falling in older community-dwelling adults but moderate exercise adherence [34].

The physiotherapists that implement the Otago programme are trained in a half-day basic training. The training consists of information about the Otago programme and how to deliver it to the patients with the original recommendations of [name] and Robertson [57]. In this training emphasis is put on prescription and control of the exercises. The physiotherapists will adapt the programme at every home session. The implementation of the Otago programme is similarly planned as the T&E program: eight home session and four phone calls in six months. At each session the physiotherapists revise the exercises execution, verify that the diaries are correctly completed and repeat the recommendations for the training. At each phone call, the physiotherapists ask about the exercises, if the patient encounter difficulties and encourage them to train themselves.

The second intervention (“Helsana”) is considered as usual care. It consists of a booklet with safety advice and twelve exercise-cards for “Going safely”, as constructed by the Swiss health care insurance Helsana. Helsana agreed to the use of their programme in this study (no financial support was provided). It contains five exercises in sitting position; six exercises in standing position and one stand up exercise. This programme is self-directed. It has never been evaluated in a trial. Physiotherapists will demonstrate the programme during one home session while they explain the recommendations and they will do all the exercises with the patient to ensure the security. They will then call the patients four times in a six-week interval, to ask if they encounter problems with the exercises.

In cases where the practice of home-based exercises could potentially harm the patients, the local coordinator could exclude the patients of the trial.

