
Quality of life will be measured with the French and German version of the “Older People’s Quality of Life Questionnaire” OPQOL-35 [82]. The questionnaire consists of 35 items measuring quality of life based related to eight domains: 1: Life overall (4Q), 2: Health (4Q), 3. Social relationships (8Q), 4: independence, control over life, freedom (5Q), 5: home and neighbourhood (4Q), 6: Psychological and emotional well-being (4Q), 7: Financial circumstances (4Q) and 8: Culture and religion (2Q). The score ranges from 35 to 175: as higher the score, as better the quality of life.

Adherence to exercise will be prospectively assessed in monthly training diaries during 12 months where date, duration, type of exercises (including walking) and intensity of effort are noted. To ensure that the patients complete the diaries, the physiotherapists will check them at each visit and ask about the diaries during each phone call.

Confounding factors, like life situation, living place, physical activity habits and comorbidity will be documented at each assessment session.

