### Adverse events

Because the participants of this study are older adults at risk of falling, they can experience falls or other health diseases due to the old age. If the patient, members of his family, any caregiver or the physiotherapist notes an AE like:

- Falls that require medical attention.

- Exacerbation of a pre-existing illness.

- Increase in frequency or intensity of a pre-existing episodic event or condition.

- Condition detected or diagnosed after the intervention, even though it may have been present prior to the start of the study.

- Continuous persistent disease or symptoms present at baseline that worsen following the start of the study.

they will inform the local investigator as soon as possible. The local investigator will collect the AEs with the complete description of the event on the formulary “Database for AI/AE/SAE”.

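### Non-fall adverse events are compared between arms but reported spontaneously, partly through physiotherapists who have 12 scheduled contacts in T&E and Otago and 5 in Helsana

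*Protocol article*

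**What the plan says.** **The analysis.** The Statistical analysis section of the protocol article commits to a between-arm comparison: "The proportion of adverse events (other than falls) will be compared between the groups by an external and independent statistician". It names no test.

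**The collection.** The Adverse events section begins "If the patient, members of his family, any caregiver or the physiotherapist notes an AE like" and, after a list that includes exacerbations, newly detected conditions and worsening symptoms, ends "they will inform the local investigator as soon as possible". The trigger is that someone notices an event; the physiotherapist is one of four named kinds of reporter.

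**Physiotherapist contact by arm.**
- T&E (Experimental intervention): "The implementation of the T&E programme is planned with eight physiotherapy sessions and four phone calls in six months".
- Otago (Control interventions): "eight home session and four phone calls in six months".
- Helsana (Control interventions): "Physiotherapists will demonstrate the programme during one home session", followed by four telephone calls.

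The listed content of T&E and Otago sessions is exercise execution, diary checks and training advice. Calls in all arms ask about the exercises and any difficulties or problems.

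**What is asked equally in all arms.** Under Outcomes, falls are recorded in monthly diaries for twelve months and asked about again at months 6 and 12. One general health item is also taken: "Confounding factors, like life situation, living place, physical activity habits and comorbidity will be documented at each assessment session". It is recorded as a confounder, not as adverse-event data.

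**The concern.** A comparison of adverse-event proportions is fair only if an event has the same chance of reaching the database in each arm. Here one reporting channel has, by design, more than twice as many scheduled opportunities in T&E and Otago as in Helsana. Falls, which are solicited equally in every arm, are left out of the comparison. What remains is the set of events for which the article describes no equal solicitation.

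At stake is the safety reading of both physiotherapist-delivered programmes against usual care. Equal true risks could appear as an excess in T&E and Otago, and a real excess could not be separated from better reporting.

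**Working it through.** The plan gives no adverse-event rate, capture rate or power figure for this comparison, so there is no stated figure to reproduce. The contact counts come from the article; every capture and risk value below is an assumption.

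**Step 1: contacts.**
- T&E: 8 + 4 = 12.
- Otago: 8 + 4 = 12.
- Helsana: 1 + 4 = 5.
- Ratio: 12/5 = 2.4. Adding the two blinded post-baseline assessments gives 14, 14 and 7.
- Timing: if the Helsana calls are six-weekly, the last falls at 4 × 6 = 24 weeks. If instead all four fall within six weeks, they end sooner. Either way no physiotherapist visit or call is scheduled after month 6 in any arm.

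**Step 2: capture.** Let q be the chance that one physiotherapist contact passes on a given event, k the number of contacts (taken as independent), and s the share captured by patient, family or caregiver, equal in all arms. Then

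capture = 1 − (1 − s)(1 − q)^k, with k = 12 or 5.

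| q | s = 0: 12 v 5 contacts | ratio | s = 0.5: 12 v 5 contacts | ratio |
|---|---|---|---|---|
| 0.02 | 22% v 10% | 2.2 | 61% v 55% | 1.11 |
| 0.05 | 46% v 23% | 2.0 | 73% v 61% | 1.19 |
| 0.10 | 72% v 41% | 1.75 | 86% v 70% | 1.22 |
| 0.30 | 99% v 83% | 1.19 | 99% v 92% | 1.08 |

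Example: q = 0.05, s = 0.5 gives 1 − 0.5 × 0.540 = 0.730 and 1 − 0.5 × 0.774 = 0.613, ratio 1.19.

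The s = 0 columns are the upper end, because they give the other named reporters no role. All columns also let each event meet every contact, which overstates capture in both groups. Events after month 6 meet no physiotherapist contact and so dilute the difference. If half of all events fell there, q = 0.05 and s = 0.5 would give (0.730 + 0.5)/2 = 0.615 against (0.613 + 0.5)/2 = 0.557, ratio 1.10.

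**Step 3: chance of a false signal.** Take one active arm (n = 162) against Helsana (n = 81), equal true risk, and a two-sided 5% test of two proportions. The chance of a significant excess in the active arm is Φ((d − 1.96·SE0)/SE1), where d is the difference in observed proportions, SE0 the pooled and SE1 the unpooled standard error. Without differential capture this is 2.5%.

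| Capture, active v Helsana | True risk 10% | 20% | 30% | 40% |
|---|---|---|---|---|
| 70% v 60% | 4% | 6% | 8% | 9% |
| 80% v 50% | 12% | 23% | 36% | 50% |
| 90% v 40% | 27% | 55% | 78% | 92% |

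Example: 80% v 50% at 20% risk gives 0.16 against 0.10, so d = 0.06, SE0 = 0.0472, SE1 = 0.0441, and Φ((0.06 − 0.0926)/0.0441) = Φ(−0.74) = 0.23.

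**Step 4: T&E against Otago.** Both have k = 12 and the same listed session and call content, so planned contact gives a capture ratio of 1. Events are under-counted in both, without a planned differential.

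**The case against.** The strongest objection is that this is a condensed article. The Adverse events section names a dedicated recording form that is not shown, and the case report forms for months 6 and 12 may contain an adverse-event question. That stands as a limit on wording: one can say only that the article describes no such question. It does not remove the point, because the article does state both the reporting route and the comparison, and the two together give unequal ascertainment.

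A reader might infer three stronger things that the document does not support.
- **That no scheduled visit touches on health, or that contact stops after month 6.** Comorbidity is documented at every assessment, calls ask about difficulties or problems with the exercises, and diaries on falls and training reach the coordinators to month 12. Spontaneous reports also remain possible throughout. These are partial channels rather than adverse-event collection, but they are not nothing.
- **That spontaneous reporting alone distorts the comparison.** Where it applies equally to all arms, it under-counts. The distortion comes from the unequal contact.
- **That the trial cannot compare the safety of self-selected (T&E) and prescribed (Otago) exercise.** Planned contact is the same in both, so this does not follow from contact frequency.

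It is also fair to say that non-fall adverse events are neither the primary nor a listed secondary outcome, and that the article says they are compared without stating a hypothesis test. This limits the stakes, but a between-arm difference would still be read as safety evidence.

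**Conclusion.** The point holds for the contrasts of T&E and Otago with Helsana. Following the stated rules, a named reporter has 12 scheduled contacts in each physiotherapist-delivered arm and 5 in Helsana, so equal true risks would tend to appear as an excess against Helsana.

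The direction follows from the design; the size does not. Over the assumed values, the apparent ratio runs from about 1.1 to 2.2. It shrinks as patient, family and caregiver reports capture more, and as more events fall after month 6. The false-signal chance is modest at 70% v 60% capture and substantial at 80% v 50% or wider. T&E against Otago, and the second half-year in all arms, suffer mainly from under-counting.

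The conclusion assumes that no form outside the article already asks about adverse events identically in all arms. The change is worth making because it is cheap.

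**What to change.** Add one structured question on new or worsened health conditions since the last assessment to the existing 6- and 12-month blinded assessments, worded identically in all arms. State that the between-group comparison of non-fall adverse events uses these solicited events. For participants already past a visit, or as an alternative to a new item, derive new or worsened conditions from the comorbidity record taken at each assessment. Continue to collect spontaneous reports for safety handling, and list them descriptively by arm without a between-group test.

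The cost is one item at two existing visits and a sentence in the analysis section. There are two small downsides. Six-month recall will miss minor events, though the question and recall period are the same in every arm. The question must also be worded so that it does not lead participants to reveal their programme to the blinded assessor, since blinding relies on their not discussing treatment. If an existing form already asks such a question in all arms, it is enough to say so and base the comparison on it.
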